# Enhancing Recruitment Using Teleconference and Commitment Contract (ERUTECC): study protocol for a randomised, stepped-wedge cluster trial within the EFFECTS trial

**DOI:** 10.1186/s13063-017-2367-8

**Published:** 2018-01-08

**Keywords:** Stroke, Randomised controlled trial, RCT, Recruitment, Randomised stepped-wedge cluster trial

## Abstract

**Background:**

Many randomised controlled trials (RCTs) fail to meet their recruitment goals in time. Trialists are advised to include study recruitment strategies within their trials.

EFFECTS is a Swedish, academic-led RCT of fluoxetine for stroke recovery. The trial’s primary objective is to investigate whether 20 mg fluoxetine daily compared with placebo for 6 months after an acute stroke improves the patient’s functional outcome. The first patient was included on 20 October 2014 and, as of 31 August 2017, EFFECTS has included 810 of planned 1500 individuals. EFFECTS currently has 32 active centres.

The primary objective of the ERUTECC (Enhancing Recruitment Using Teleconference and Commitment Contract) study is to investigate whether a structured teleconference re-visit with the study personnel at the centres, accompanied by a commitment contract, can enhance recruitment by 20% at 60 days post intervention, compared with 60 days pre-intervention, in an ongoing RCT.

**Methods:**

ERUTECC is a randomised, stepped-wedge cluster trial embedded in EFFECTS. The plan is to start ERUTECC with a running-in period of September 2017. The first intervention is due in October 2017, and the study will continue for 12 months. We are planning to intervene at all active centres in EFFECTS, except the five top recruiting centres (*n* = 27). The rationale for not intervening at the top recruiting centres is that we believe they have reached their full potential and the intervention would be too weak for them. The hypothesis of this study is that a structured teleconference re-visit with the study personnel at the centres, accompanied by a commitment contract, can enhance recruitment by 20% 60 days post intervention, compared to 60 days pre-intervention, in an ongoing RCT.

**Discussion:**

EFFECTS is a large, pragmatic RCT of stroke in Sweden. Results from the embedded ERUTECC study could probably be generalised to high-income Western countries, and is relevant to trial management and could improve trial management in the future. It might also be useful in clinical settings outside the field of stroke.

**Trial registrations:**

The ERUTECC study was registered in the Northern Ireland Hub for Trials Methodology Research Studies Within a Trial repository (SWAT58) on 30 April 2017.

ClinicalTrials.gov, ID: NCT02683213. Retrospectively registered on 2 February 2016.

**Electronic supplementary material:**

The online version of this article (doi:10.1186/s13063-017-2367-8) contains supplementary material, which is available to authorized users.

## Background

### Introduction

Many randomised controlled trials (RCTs) fail to meet their recruitment goals in time [1, 2]. A study of 114 multicentre trials in the UK showed that 45% failed to reach 80% of their recruitment goal. Less than one third of the trials recruited their original target number of participants within the time originally specified, and around one third had to be extended in terms of time and resources [3], and it has been identified as the highest priority to find methods to enhance recruitment to the RCT [4]. There are a few trials that have sought to evaluate different strategies for recruiting patients. However, these studies are small, and some are hypothetical, making the interpretation unclear [5]. Qualitative interventions within trials to improve recruitment have been developed in the UK [6], and in addition, online resources [7, 8] are available. In spite of that, we need to know more about the barrier and success factors for trials in recruiting patients and especially in RCTs. Given these facts, trialists are advised to include study recruitment strategies within their trials [5].

One alternative is to embed trials of recruitment interventions within host trials. An embedded recruitment trial is defined as [9]:‘…a RCT in which an intervention (or several interventions) to enhance recruitment outcomes are tested in the context of another RCT (or several RCTs) known as the host RCT(s)’.

The EFFECTS (Efficacy oF Fluoxetine – a randomisEd Controlled Trial in Stroke, Clinical Trials number NCT02683213) study seeks to investigate whether 20 mg fluoxetine daily compared with placebo for 6 months after acute stroke improves patients’ functional outcome [10]. The EFFECTS study is a multicentre trial aiming to recruit 1500 patients in Sweden. The study collaborates with two other investigator-led studies, FOCUS (UK) and AFFINITY (Australia/New Zealand/Vietnam). Each trial is funded independently and intends to report its own results [10].

The first patient in EFFECTS was included on 20 October 2014. Our primary recruitment goal was that each centre should randomise at least two patients per month. In reality, there are huge differences between centres regarding recruitment. Looking back between June 2016 and May 2017, for instance, only three centres have achieved the recruitment goal: Danderyd Hospital, Karolinska University Hospital Solna and Sundsvall Hospital, while another three (Mora General Hospital, Alingsås General Hospital and Skaraborg Hospital Skövde) came close. In fact, these six centres have so far included half of the individuals. This pattern – that a few centres have included the majority of individuals – has been consistent since the start, irrespective of different strategies. The recruitment rate per month and centre is updated in real time and is available in the public domain [11].

### Rationales for the study

Currently, the EFFECTS trial includes 30 patients per month [11], and recruitment projections would take the trial beyond its current funding. Thus, a new strategy is needed.

After talking to the principal investigators (PIs) at the centres, and to trialists in the UK with similar studies, we are confident that five of the top recruiters (Danderyd Hospital, Karolinska University Hospital Solna, Sundsvall Hospital, Mora General Hospital and Skaraborg Hospital Skövde) have reached their full potential, and little would be gained from the planned intervention.

We have asked the centres via a survey, and have also discussed this in person at investigator meetings, what they consider to be the most important barrier to recruitment for trials. They have said that the most important barrier is the lack of time for the physician responsible to identify the right patients and to carry out the study-specific procedures at baseline. The second most important factor is the lack of time for all other study personnel. They have a high clinical workload at their clinic and do not have any time specifically dedicated to working with clinical trials. It is the head of department (verksamhetschef) who is responsible for finances and personnel. Without the support of the head of department there will hardly be any change in recruitment. We will, therefore, invite the head of department (verksamhetschef) at the local centre to the teleconference in addition to the PI and the research nurse. Hopefully, we can work together to identify what could be done to provide more opportunities at the clinic to do research for both physicians and nurses within working hours. We have chosen a teleconference because it is time effective and less expensive than a face-to-face meeting. In addition, we hypothesised that a commitment contract would make it more personal for the local centre.

We have followed the 2013 SPIRIT (Standard Protocol Items: Recommendations for Interventional Trials) Checklist [12] in conjugation with the 2013 SPIRIT explanation and elaboration guidance for protocols of clinical trials [13] (Additional file 1).

### Objectives of the study

#### Primary objective

The primary objective of this study is to investigate whether a structured teleconference re-visit with the study personnel at the centres, accompanied by a commitment contract, can enhance recruitment by 20% during 60 days post intervention, compared with 60 days pre-intervention, in an ongoing RCT.

#### Secondary objectives

Recruitment rate 61–120 days post teleconferenceWe will compare the recruitment 60 days post teleconference with a baseline inclusion from 1 Sep 2017 to 31 Oct 2017 for all centres. The purpose is to see if there is any bias or impact during the course of the study

The secondary objective must be seen as exploratory due to low power.

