### The rationale for the trial design

We have chosen the stepped-wedge cluster randomised study design [14] for three reasons. First, it is not possible for us to carry out the intervention at 14–15 centres at the same time. Second, we believe that all medium and low recruiting centres could gain from the intervention, and in a stepped-wedge cluster design all centres are exposed. Every step provides before and after observations, and every step switches from control to become exposed to the intervention. Third, we have noticed a seasonal variation in recruitment. During the Christmas and Easter holidays, and especially during the summer, recruitment is falling. This intervention gives a realistic view of recruitment throughout the whole year. To the best of our knowledge, only one randomised stepped-wedge study in the field of stroke has been done [15].

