### Study type

We will use a randomised, stepped-wedge cluster design, where every step provides data before and after intervention, but not at the same point in time.

Figure 2 illustrates the stepped-wedge cluster study in our study. As the name indicates, the intervention has 11 different steps, and the schema takes the form of a wedge. Figure 3 is a schematic diagram of the time schedule of enrolment, interventions (including any run-ins and washouts) and assessments for the participating centre.

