**Fig. 3 Fig3:**
[figure not shown]
The flow of participants in the ERUTECC study. In ERUTECC, each centre follows the same flow, with a 60-day period of running in, and a 60-day post-intervention period (teleconference). The figure shows one step. We will add up all patients for all 11 steps in the 60-day running-in period and compare this with the inclusion rate for all centres’ 60-day post randomisation period

In ERUTECC, all centres have a 60-day running-in period and a 60-day post-intervention period. Our plan is to start in September 2017 and finish in October 2018.

The 27 sites will be divided into two categories: medium and low recruiters. The rationale for this is that we do not want to risk all medium recruiters falling into the same step, for example the summer period, which usually a low-recruiting period. The centre will be randomised in terms of the order in which intervention will be performed, leading to (at least) one medium and (at least) one low recruiter in each of the 11 steps (Fig. 2).

All centres in the EFFECTS study, their classification, type and numbers of patients are listed in Table 1.

**Table 1 Tab1:** Centres in EFFECTS as of 31 August 2017

Centre	Type of centre	Number of stroke patients per year^a^	First included patient in EFFECTS (yyyy-mm-dd)	Total number of patients recruited	Percentage of number of patients recruited^b^
01 Danderyd Hospital	SU at hosp	837	11/11/2014	110	14%
02 Karolinska University Hospital Solna	SU at univ hosp	542	10/20/2014	98	12%
03 Skaraborg Hospital Skövde	SU at hosp	422	10/20/2014	56	7%
04 Hässleholm Hospital	SU at hosp	203	3/23/2015	32	4%
05 Uppsala University Hospital	SU at univ hosp	496	4/20/2015	39	5%
06 Karolinska University Hospital Huddinge	SU at univ hosp	488	4/8/2015	15	2%
07 Mora General Hospital	SU at hosp	226	4/15/2015	49	6%
08 Falu General Hospital	SU at hosp	510	5/13/2015	12	1%
09 Lidköping	SU at hosp	162	10/6/2015	12	1%
10 Capio St Göran’s	SU at hosp	697	6/24/2015	51	6%
11 Visby General Hospital	SU at hosp	132	11/4/2015	7	1%
12 Norrland University Hospital	SU at univ hosp	355	9/22/2015	12	1%
13 Kristianstad Central Hospital	SU at hosp	334	9/24/2015	11	1%
14 Norrtälje Hospital	SU at hosp	165	12/9/2015	1	0%
15 Helsingborg General Hospital	SU at hosp	391	11/18/2015	15	2%
16 Skåne University Hospital Malmö	SU at univ hosp	478	12/18/2015	16	2%
17 Halland Hospital Halmstad	SU at hosp	374	12/1/2015	36	4%
18 Mälar Hospital Eskilstuna	SU at hosp	246	2015-22-23	10	1%

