## Trial status

The main study – EFFECTS – included its first patient on 20 October 2014, and as of 31 October 2017, 881 patients have been included. The last patient is estimated to be recruited in March 2019, with the last follow-up 1 year later. The ERUTECC will start in November 2017 (Fig. 2) and continue for 1 year.

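### The secondary comparison sets post-teleconference windows spread over a year against one autumn baseline, so season biases it downward and it cannot separate bias or impact from season

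*Protocol article*

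**What the plan says.** Under Secondary objectives the protocol article will "compare the recruitment 60 days post teleconference with a baseline inclusion from 1 Sep 2017 to 31 Oct 2017 for all centres". The aim is stated next: "The purpose is to see if there is any bias or impact during the course of the study". The only caution is "The secondary objective must be seen as exploratory due to low power"; season is not mentioned there.

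Elsewhere the article treats season as a known feature of recruitment. In The rationale for the trial design it reports: "During the Christmas and Easter holidays, and especially during the summer, recruitment is falling". The text under Fig. 3 explains that centres were stratified so that the medium recruiters would not all fall in one step, "for example the summer period, which usually a low-recruiting period".

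For the calendar, Study type says that "the intervention has 11 different steps". Explanation of the randomised, stepped-wedge design starts step 1 in September 2017, with its teleconference at the end of October, and starts step 2 one month later. Each step has 60 days before and 60 days after the teleconference. The text under Fig. 3 gives October 2018 as the finish.

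**The concern.** The comparator is two autumn months with none of the holiday periods that the article names. The post-teleconference windows contain all of them. With no effect, no contamination and no trend, the pooled contrast would still be expected to fall below 1. The time gap also grows with each step, so any drift in the host trial enters as well.

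The contrast is meant to reveal bias or impact. A shortfall could instead be season or trend, and a real gain would look smaller than it is. A reader who set it beside the primary result could take the gap between the two as a sign of bias in the primary analysis, when season alone would produce it. The exploratory label does not cover this: low power is a matter of imprecision, and this is a systematic shift.

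**Working it through.** **1. Calendar.** Number the months from September 2017 = 1. Step *s* has its run-in in months *s* and *s*+1 and its post window in months *s*+2 and *s*+3. Step 1 then has September-October before and November-December 2017 after. Step 11 has July-August before and September-October 2018 after, which reproduces the stated finish. The article gives no expected value for the secondary contrast, so there is no further figure to reproduce.

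**2. Months covered (11 steps × 2 = 22 step-months on each side).**

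| Window | Months and number of times counted |
|---|---|
| Fixed baseline | Sep and Oct 2017 |
| Post windows | Nov 2017 once; each month Dec 2017 to Sep 2018 twice; Oct 2018 once |
| Run-ins (primary comparator) | Sep 2017 once; each month Oct 2017 to Jul 2018 twice; Aug 2018 once |

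Six of the 22 post step-months are June to August, reached by steps 7 to 10. December is in steps 1 and 2. March-April, where Easter falls, is in steps 4 to 6. Only step 11 has a post window that matches the baseline in season. The downward direction follows from this layout and the article's own statement on season, with no assumed number.

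**3. Size, under assumed dips.** The article gives no amplitude. Two patterns are assumed, with September-October = 1 and equal weight per step:

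- Mild: December -15%; March, April and June -5% each; July -25%; August -10%.
- Strong: twice those values (-30%; -10% each; -50%; -20%).

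Null ratio against the fixed baseline = 1 - (sum of dips over post step-months)/22:

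- Mild: 2 × (0.15 + 0.05 + 0.05 + 0.05 + 0.25 + 0.10) = 1.30; 1 - 1.30/22 = 0.941.
- Strong: 1 - 2.60/22 = 0.882.

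In the run-ins August counts once instead of twice, so the sum is 1.20 (mild) or 2.40 (strong). The null ratio in the primary pairing is:

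- Mild: (1 - 1.30/22)/(1 - 1.20/22) = 0.941/0.945 = 0.995.
- Strong: (1 - 2.60/22)/(1 - 2.40/22) = 0.882/0.891 = 0.990.

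A true 20% rise would show in the secondary contrast as 1.20 × 0.941 = 1.13 (mild) or 1.20 × 0.882 = 1.06 (strong).

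**4. Sensitivity to the assumed pattern.** Other patterns (July-August only; June-August; either of these with half the dip in December and April), with summer dips of 10% to 50%, give null ratios of 0.98 to 0.82. The primary pairing stays between 0.97 and 1.00. A true 20% rise turns negative only in the most extreme case (50% in June-August with 25% in December and April): 1.20 × 0.818 = 0.98.

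**5. Trend.** The gap from the baseline to the post window is *s*+1 months: 2 for step 1, 12 for step 11, and 7 on average. In the primary pairing it is 2 months at every step.

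**6. A minor point.** 1 September to 31 October is 61 days. If counts rather than rates are compared, 60/61 = 0.984 adds a further 1.6% deficit.

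**The case against.** **The baseline has a real merit.** It precedes every teleconference. The Problems section fears that waiting centres may hear of the intervention and change their behaviour early; that could affect later run-ins but not this baseline. This stands, and it is a reason to keep the baseline. It does not remove the seasonal imbalance.

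**The effect is small against chance.** Removing the five top centres (379 inclusions) and the three closed ones (24) from 810 leaves 407. If that share held for the 881 - 810 = 71 inclusions of September-October 2017 (an assumption), the baseline would be about 71 × 407/810 = 36 patients, with a Poisson standard error of 1/√36, or about 17%. A shift of 6% to 12% is 2 to 4 patients. This also stands and keeps the point modest. But the seasonal shift has a known direction, and the stated caveat does not warn of it.

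**The text can be read otherwise.** It might mean step-by-step inspection, or days 61-120, or a run-in that begins in November 2017, since Trial status says the study will start then. Inspection by step would help, and step 11 is matched in season. Under the other two readings the windows still span about a year against two autumn months. An analysis plan that is not shown might adjust for season; the comparison as fixed in the article does not.

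**Two stronger readings are tempting and not supported.** A reader might infer that the check would show no gain, or a loss, whether or not the intervention works. Under the mild and strong patterns a true 20% rise still appears as a gain. A reader might also set the 71 inclusions, 35.5 per month, from "as of 31 October 2017, 881 patients have been included" and the 810 at 31 August against "Currently, the EFFECTS trial includes 30 patients per month", and read 30/35.5 = 0.845 as a 15% fall to come. Those counts cover the whole host trial, including the excluded top centres. The 95% Poisson interval for the monthly rate, 27.7 to 44.8, includes 30. The comparison is compatible with chance and is not evidence of season.

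**Conclusion.** The point holds for the pooled secondary contrast. Its direction, downward, follows from the article's calendar and its own account of season. Its size is not documented: the null ratio is about 0.94 under mild and 0.88 under strong assumed dips, with equal weight per step. A true 20% rise is then attenuated to about +13% or +6%, not reversed. A very large change would still be visible, but a moderate one could not be told from season or from up to a year of trend. The primary pairing is almost untouched by the same patterns (0.995 and 0.990), so the article's main result is not in question here. Because the objective is secondary and exploratory, this should be corrected, but it does not threaten the trial.

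**What to change.** Keep the September-October 2017 baseline as the reference that no teleconference can have contaminated, and make three changes to the wording of the analysis.

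- Adjust the contrast for calendar month. Not-yet-exposed centre-months alone will not suffice: only steps 10 and 11 are unexposed in July 2018, only step 11 in August, and none in September-October 2018. Add the same centres' host-trial recruitment in earlier years, and use the five non-intervened top centres as a concurrent series.
- Report the contrast by step, so that the season-matched step 11 and the summer steps can be seen separately.
- Label it descriptive because of seasonal confounding as well as low power.

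The host trial's randomisation system already holds the data, so the cost is a little more analysis work. The seasonal estimates will be imprecise: four of the 27 centres included their first patient only in 2017 (Table 1) and have no complete earlier year. Use of the top centres assumes that they share the seasonal pattern of the others, which should be stated.

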### Hypothesis

Does a structured teleconference re-visit with the study personnel (PI, at least one research nurse, and the head of department) at the centres, accompanied by a commitment contract, enhance recruitment by 20% during 60 days post intervention, compared with 60 days pre-intervention in the EFFECTS study?

### The rationale for the trial design

We have chosen the stepped-wedge cluster randomised study design [14] for three reasons. First, it is not possible for us to carry out the intervention at 14–15 centres at the same time. Second, we believe that all medium and low recruiting centres could gain from the intervention, and in a stepped-wedge cluster design all centres are exposed. Every step provides before and after observations, and every step switches from control to become exposed to the intervention. Third, we have noticed a seasonal variation in recruitment. During the Christmas and Easter holidays, and especially during the summer, recruitment is falling. This intervention gives a realistic view of recruitment throughout the whole year. To the best of our knowledge, only one randomised stepped-wedge study in the field of stroke has been done [15].

## Methods

### Study settings

EFFECTS has been running for almost 3 years, and we know the recruitment rate per centre and month. Initially we had 35 centres. Three centres – Karolinska Hospital Huddinge, Visby General Hospital and Högsbo Rehabilitation Hospital – have been closed due to low recruitment mainly because of a lack of PI. Of the 32 centres, we have identified five centres that have achieved our goal, that is recruiting two or more patients per month. They are the top recruiters: Danderyd Hospital, Karolinska University Hospital Solna, Skaraborg Hospital Skövde, Mora General Hospital and Sundsvall Hospital. We will not intervene at these centres because we believe that they have reached their full potential and the intervention is too weak for them. Not including the top recruiters, this leaves us with 27 centres in this study.

Figure 1 shows a Consolidated Standards of Reporting Trials (CONSORT) flow diagram [16] of the study. Hence, ERUTECC is a randomised, stepped-wedge cluster design [14] study. We made some minor changes to the CONSORT flow diagram layout.

